### Intervention

All included participants will receive: 1) verbal and written counselling about the current best-practice approach for the treatment of mTBI that consist of gradual cognitive and physical activity that do not result in symptoms exacerbation and 2) individualized recommendations about cognitive and physical activation. A neurocognitive assessment and an exercise tolerance assessment will be used to provide the individualized recommendations regarding gradual cognitive and physical activation. A neuropsychologist will proceed to a clinical neuropsychological assessment of anxiety, attention and executive function using the following tests: Hospital anxiety and depression scale [28], Working memory index and Processing speed index of the WAIS-IV [29], Conners’ Continuous Performance Test 3 [30]. Advice will be provided based on the clinical evaluation results regarding an individualized step-by-step graded exposition to cognitive stimulus guided by symptoms evolution. A follow-up assessment by the neuropsychologist will be held after 6 weeks and advice will be given according to the results of this follow-up assessment. A kinesiologist will also evaluate the symptomatic response to cardio-vascular exertion. The result of this evaluation will be used to provide each participant with a graded physical exercise program aiming for sub-symptoms exacerbation.

#### Control group – gradual SPA program

The subjects in this group will take part in 8 in-clinic cardiovascular exercise sessions in a 6-week period supervised by a kinesiologist (30 to 45 min each session). If the symptoms disappear within the treatment period, the subject will be evaluated for clearance.

#### Experimental group – individualized gradual SPA combined with cervicovestibular rehabilitation program

Two physiotherapists (instead of a kinesiologist for the control group) will supervise the 8 treatment sessions (30 to 45 min each session) according to an individualized care program which will include a cervical and/or vestibular rehabilitation program, as well as the cardiovascular exercise component. The participant will also perform a home cervicovestibular specific-exercise program once a day. The first physiotherapist will be an expert in manual physical therapy. The physiotherapist will evaluate the physical dysfunctions associated to mTBI with a standardized evaluation to build the treatment plan. Cervical and upper cervical range-of-motion and segmental mobility testing using passive physiological intervertebral motion testing for pain reproduction and mobility assessment will be used. Measures of intervertebral mobility assessment have been shown to be reliable at the cranio-vertebral region (Kappa from 0.81 to 0.83) [31]. Segmental mobility testing is reliable at the cervical spine for mobility when combined with pain reproduction (Kappa 0.79 to 0.96) [32]. Muscle strength and coordination will also be assessed using the cranio-cervical flexion test [33]. Temporomandibular function will be assessed for mobility and pain response as described in VonPiekarts and Ludtke trial [34]. Cervical spine proprioception will be evaluated if deemed necessary clinically using the cervical rotation joint position error test [35]. Finally, vestibulo-ocular function using the Vestibular/Ocular Motor Screening (VOMS) [8], head trust, Dix Hallpike and balance using the Balance Error Scoring System (BESS) [36] will be assessed at the first session to create the treatment plan. The physiotherapist will provide cervical and upper cervical mobilisations and manipulation. The mobilisation techniques will be chosen by the physiotherapist according to the results of the examination performed at the beginning of each session with the segmental manual testing procedure described above. The physiotherapists will be allowed to use any of the following manual therapy techniques: cranio-vertebral flexion or extension, rotations at any levels, lateral glides, postero-anterior glides or muscle relaxing technique at the cranio-vertebral region. At the mid and lower cervical spine, infero-medial glides, supero-anterior glides mobilisations or muscle relaxing technique will be used if deemed clinically relevant as described in a previous trial [24]. The therapeutic exercises will consist of range of motion, neuromotor retraining of the neck stabilizers muscles and sensorimotor retraining exercises based on the best current clinical approach for neck pain and cervicogenic headache and according to the impairment specifically found on each patient [14, 16, 37, 38]. The second physiotherapist, will be a vestibulo-ocular expert physiotherapist. He will provide treatment consisting of the canalith repositioning manoeuvre, vestibular adaptation, ocular motor exercises, balance and/or habituation exercises [39, 40]. The vestibular treatment will also be adapted by the treating physiotherapist to the individual participant according to the impairment found at the initial evaluation. Education on concussion and on the neurophysiology underlying their symptoms will be given to participants by the therapist. The number of treatments given by each physiotherapist will vary among participant according to findings at the clinical evaluation but will be limited to a maximum of 8 treatment sessions (30 to 45 min each treatment). Patients in this group will also perform the graded SPAprogram according to the initial kinesiologist recommendation and supervised by the physiotherapist. If the symptoms disappear within the treatment period, the subject will be evaluated for clearance to return to usual activities. Adherence to treatment will be recorded by the treating therapists and a logbook will be completed by the participants each week to record home exercises performed. All participants will be advised to avoid concomitant interventions. If a concomitant intervention is used, it will be recorded by the treating therapist. Table 2 describes every intervention step that both groups will achieve.

**Table 2 Tab2:** Description of the intervention

Control – SPA program	All subjects: Neuropsychologist and kinesiologist advice	Control: Cardiovascular program only - 8 sessions	All subjects: Follow-up by the neuropsychologist for final advice
Intervention - SPA + cervicovestibular program		Intervention: Cervicovestibular physiotherapy and cardiovascular program - 8 sessions	

### The primary outcome measure

#### *Post-Concussion Symptoms Scale (PCSS)*

The severity and impact of symptoms will be measured by a self-reported scale, the PCSS [41]. This scale is a list of 22 symptoms for which participant rate each symptom for severity on a 0 (none) to 6 (severe) numerical scale. The maximum possible score is 132 (22 × 6 = 132). This valid and reliable scale has a minimal detectable change (90% confidence interval) of 12.3 PCSS points [22]. Normative values have been established [41]. The symptoms list can be divided in four main sub-groups (physical, cognitive, emotional and sleep disorders) and analysed accordingly [5].

### Secondary outcome measures

The secondary outcome measures will include: Clearance to return to pre-injury function without restriction, Numerical Pain Rating Scale, Neck Disability Index, Dizziness Handicap Inventory, Headache Disability Index, number of recurrent episodes and global rating of change.

#### Clearance to return to function

The number of days between the initial evaluation, the date of the trauma and the full clearance to return to function (work, study or physical activity/sport) will be measured. The clearance to return to function will be determined by the treating therapist and the neuropsychologist. The treating therapist (physiotherapist or kinesiologist according to which group the patient will be allocated to) will use the stepwise progression from the 5th International Consensus Statement on Sport Concussion [5]. As patients achieve the last step of this progression, indicating that the patient can safely return to play, the neuropsychologist and the kinesiologist will confirm this decision with a structured interview (neuropsychologist) and an ergocycle aerobic test (kinesiologist). The clearance will be determined by the day for which 1) the symptoms will have return to usual level 2) the neurological, cervical spine and vestibular impairments found at the beginning of the study will be considered in the normal range by the treating therapist 3) the subject returned to his normal level of all functional activities.

#### Numerical pain rating scale (NPRS)

The level of neck pain and headache will be captured separately with NPRS. Using an 11-point scale, ranging from 0 (no pain) to 10 (worst pain imaginable), participants will be asked to answer the following question: “On a scale of 0 to 10, where 0 corresponds to no pain and 10 to the worst imaginable pain, evaluate the intensity of your neck pain at this moment”. The same question will be asked for the headache. The NPRS is moderately reliable (Intraclass Correlation Coefficient [ICC] = 0.76) and has a clinically important difference of 13% [42].

#### Neck disability index (NDI)

The NDI is a 10-item questionnaire that measures a patient’s self-reported neck pain related disability. Questions include pain and activities of daily living. The questions are measured on a six-point scale from 0 (no disability) to 5 (full disability). The numeric response for each item is summed for a total score ranging from 0 to 50. The reliability (ICC: 0.73 to 0.98), construct validity, and responsiveness to change have all been demonstrated in various populations [43]. The validated French version NDI will be used [44].

#### Headache disability inventory (HDI)

The HDI is a 25-item questionnaire measuring the disability related to patient reported headache. Questions include activities of daily living and perceived disability as measured with an ordinal scale (yes (4 points), sometimes (2 points), no (0 point)). After adding every numerical score, the total score is on 100 for which 0 means no disability and 100 complete disability. The test-retest reliability (r = 0.79 to 0.83) and the minimal detectable change (16 points) are known [45].

#### Dizziness handicap inventory (DHI)

The DHI [46] is a 25-items questionnaire that identifies the degree of perceived difficulty a patient may experience as a result of dizziness or unsteadiness. The items are sub grouped into three content domains representing functional, emotional, and physical aspects of dizziness and unsteadiness [46]. The questionnaire demonstrated high Test-retest reliability (r = 0.92 to 0.97) and internal consistency (α = 0.72 to 0.89) [47].

#### Recurrent episodes

The number of recurrence episodes was calculated as the number of episodes of symptoms with a duration of at least 48 h following a trauma during the 26 weeks of the study.

#### Global rating of change

GRC questions are designed to quantify a patient’s perceived improvement or deterioration over time. Using a 15-point GRC scale, ranging from − 7 (a very great deal worse) to 0 (about the same) to + 7 (a very great deal better), participants will be asked to answer the following question: “Overall, has there been any change in your condition since the initial evaluation? Please indicate if there has been any change in your condition by choosing one of the following options [48].” The validity, reliability (ICC = 0.90) and responsiveness of GRC scales have been established [49].

### Statistical analyses

Descriptive statistics will be used for all outcome measures at each measurement time to summarize results. Baseline demographic data will be compared (independent *t*-test and Chi-squared tests) to establish the comparability of groups. All data will be tested to check the distributional assumptions for the inferential statistical analyses. An intention-to-treat analysis will be used in which all participants will be analysed in the group to which they were originally assigned. Per protocol analysis will also be performed. All dropouts and the reason for dropping out of the study will be reported. Any harm or unintended effects during the programs will be recorded. A 2-way ANOVA (2 Groups [Group 1 or 2] × 4 Time [week 0, 6, 12, 26]) will be used to analyse the effects of the rehabilitation programs on the primary outcome and on most of the secondary outcomes (SPSS 22, proc. GENLIN). We expect no group effects, as the groups should be equal at baseline. A time effect should be observed, as both groups should improve given they will both receive an interventions. Finally, we expect a significant Time x Group interaction since the groups should react differently over time, ***with a faster recovery for the Experimental group mainly seen at week 6 and 12***. This will be statistically detailed with post-hoc tests (Bonferroni correction). An independent t-test will be used to analyse the effects of the rehabilitation programs on clearance to return to function.

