
### Objectives and hypothesis

The primary objective of the current RCT is to compare the addition of a 6-week individualized gradual SPA program combined with cervicovestibular rehabilitation program to a gradual SPA program alone in adults with subacute (> than 3 weeks post mTBI) headache, neck pain and /or dizziness-related to mTBI on the severity and impact of symptoms as measured by the Post-Concussion Symptoms Scale (PCSS). The secondary outcomes will be: time for clearance to return to usual activities, number of recurrence episode within 26 weeks after the treatment phase, functional level, intensity of neck pain, headache and dizziness. As SPA is well recognised for the treatment of persistent PCS [5], it supports the choice of using SPA as the comparator intervention in the present study. Our hypothesis is that the individualized SPA combined with cervicovestibular rehabilitation program will improve overall symptoms, time to return to activities as well as function faster and to a greater extent than the conventional approach and between group differences will be observed at week 6 and 12.

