### Population

Forty-six adults with a diagnosis of mTBI (based on the definition of McCrory et al.) [5] and symptoms of dizziness, neck pain and/or headaches (reported on the PCSS) [21] lasting for more than 3 weeks will be recruited. Sample size calculation is based on changes evidenced by the PCSS for individuals with mTBI. According to sample size calculation (G*Power 3.1.9.2; α = 0.05, effect size = 0.8, power [1-β] = 0.80, SD = 20.0 PCSS points, MDC = 12.3 PCSS points [22], 10% attrition), a minimum of 23 subjects is needed in each group. The expected attrition (10%) is based on the drop-rate in previous RCT from our group [23–26] and is more than the observed drop-out in similar studies in this population (6% [19] and 2% [20]). Therefore, 46 participants with mTBI will be recruited. Potential participants will be recruited at *Clinique Cortex* (an interdisciplinary concussion clinic specialized in the management of mTBI; 500 new patients with mTBI are evaluated every year), in medical clinics around Quebec City, and through the electronic mailing list of the students and employees at *Université Laval* (> 52,000 individuals).

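### The PCSS analysis is neither baseline-adjusted nor tied to a contrast at weeks 6 and 12; a baseline-adjusted comparison would gain power at no cost in patients

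*Protocol article*

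**What the plan says.** Statistical analyses gives the model for the PCSS and most secondary outcomes: "A 2-way ANOVA (2 Groups [Group 1 or 2] × 4 Time [week 0, 6, 12, 26]) will be used". It states three expectations. There should be no group effect ("We expect no group effects, as the groups should be equal at baseline"), there should be a time effect, and the benefit should appear as an interaction: "Finally, we expect a significant Time x Group interaction since the groups should react differently over time". It adds "This will be statistically detailed with post-hoc tests (Bonferroni correction"), and places the faster recovery mainly at weeks 6 and 12. Objectives and hypothesis names the same two visits: "between group differences will be observed at week 6 and 12".

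No baseline covariate is named. No contrast is singled out as primary. Neither the type of post-hoc contrast nor the number of comparisons is given.

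The Population section sizes the trial with "α = 0.05, effect size = 0.8", "power [1-β] = 0.80", an SD of 20 points and 10% attrition, and arrives at 23 per group.

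**The concern.** The hypothesis concerns two visits. The headline test concerns any departure from parallel profiles over four visits, one of which precedes treatment. Baseline PCSS is measured in everyone, yet it enters as a response and is not used to reduce the variance of the follow-up comparisons. In a trial of 46 people that precision matters: a real benefit at week 6 or 12 could be missed. Conversely, a significant interaction need not reflect the hypothesis, because a difference at week 26 alone can produce it.

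The sentence about the group effect is also wrong. In this model the group main effect averages all four visits, so equality at baseline is no reason for it to be zero.

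**Working it through.** **The plan's own figure.** A two-sample t-test with effect size 0.8, power 0.80 and one-sided alpha 0.05 needs 21 per arm. Then 21 x 1.1 = 23.1 and 21/0.9 = 23.3, which matches the stated 23. The two-sided version needs 26, or 29 with dropout. The sample size therefore belongs to a single two-group comparison, not to the interaction or to Bonferroni-split tests.

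**Inputs.** From the document: effect size 0.8, SD 20, alpha 0.05, 23 per arm, 10% attrition. Assumed: 21 completers per arm, two-sided tests, compound symmetry with visit correlation rho = 0.3 to 0.7, an equal effect at weeks 6 and 12, and a week-26 effect of zero, half (0.4 SD) or full (0.8 SD).

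**Variance of a group difference at one visit**, relative to an unadjusted comparison:

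| rho | unadjusted: 1 | change from baseline: 2(1 - rho) | baseline-adjusted: 1 - rho² |
|---|---|---|---|
| 0.3 | 1 | 1.40 | 0.91 |
| 0.5 | 1 | 1.00 | 0.75 |
| 0.7 | 1 | 0.60 | 0.51 |

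Adjustment has the smallest variance throughout.

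**The interaction alone.** It has (2 - 1)(4 - 1) = 3 df. Its noncentrality is (n/2) x sum of (d_j - mean d)² / (1 - rho), where d_j is the group difference at visit j in SD units and n/2 = 10.5. At rho = 0.5:

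- Week-26 effect zero, d = (0, 0.8, 0.8, 0): the sum is 4 x 0.16 = 0.64, noncentrality 13.44, power 87%.
- Week-26 effect half: the sum is 0.25 + 0.09 + 0.09 + 0.01 = 0.44, noncentrality 9.24, power 71%.
- Week-26 effect full: the sum is 0.36 + 3 x 0.04 = 0.48, noncentrality 10.08, power 75%.
- Effect at week 26 only, d = (0, 0, 0, 0.8): the sum is 3 x 0.04 + 0.36 = 0.48, so again 10.08 and 75%.

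The last two lines agree exactly: the test cannot tell a benefit at every follow-up visit from a benefit at week 26 alone. For the week-26-only case, power is 59% at rho = 0.3 and 94% at rho = 0.7.

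**The whole path** (simulation, 20,000 trials per row). Success means a difference declared at week 6 or week 12, with Bonferroni over those two visits. The planned path also requires a significant interaction; the adjusted contrasts do not.

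| rho | week-26 effect | interaction alone | planned, unadjusted | planned, change scores | baseline-adjusted |
|---|---|---|---|---|---|
| 0.3 | zero | 73% | 64% | 58% | 83% |
| 0.3 | half | 54% | 49% | 51% | 83% |
| 0.3 | full | 59% | 51% | 54% | 84% |
| 0.5 | zero | 87% | 70% | 75% | 89% |
| 0.5 | half | 71% | 59% | 69% | 89% |
| 0.5 | full | 75% | 61% | 70% | 90% |
| 0.7 | zero | 98% | 72% | 94% | 97% |
| 0.7 | half | 92% | 68% | 90% | 97% |
| 0.7 | full | 94% | 69% | 91% | 97% |

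Allowing a point for rounding and simulation error, the loss is about 19 to 35 points with unadjusted post-hoc tests and about 3 to 33 with change scores.

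**Without any gate**, at week 6 and alpha 0.025: the unadjusted test has 60.6% power. The baseline-adjusted test has 65.1%, 74.4% and 89.8% at rho = 0.3, 0.5 and 0.7. The loss is 4.5, 13.8 and 29.2 points.

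**Group main effect under the hypothesis.** With 0.8 SD at weeks 6 and 12 only, it is (0 + 0.8 + 0.8 + 0)/4 = 0.4 SD, or 0.4 x 20 = 8 PCSS points.

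**The case against.** A Group x Time analysis is a valid randomised comparison, and no bias is shown. Faster recovery is a statement about profiles, which an interaction addresses. Four specific points deserve an answer.

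- **The omnibus test.** A reader might infer that the 3-df interaction itself wastes the power. The figures do not support that. If the effect has gone by week 26, its power is 73-98%, and at correlations 0.5 and 0.7 it exceeds a single week-6 baseline-adjusted test at 0.05 (87% against 83%, and 98% against 94%). Nor is having baseline in the outcome vector inefficient in itself: constraining the groups to be equal there recovers about the same precision as a covariate. The plan states no such constraint.
- **The harshest reading.** Requiring the interaction, splitting alpha over four visits and counting success only at week 6 gives about 42%, 47% and 49%, against 75%, 82% and 93% for one adjusted week-6 test. The document fixes none of those choices. An interaction gate is the natural reading but is not stated, and the post-hoc tests could compare changes from baseline. The table above therefore counts either visit and splits alpha over two.
- **Week 26.** A reader might take the plan to predict no difference there. It says only that the faster recovery is seen mainly at weeks 6 and 12, which is why the week-26 effect is varied from zero to full.
- **Week 6 first.** A reader might infer that week 6 should be the gatekeeper. The document ranks neither visit above the other.

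The details of post-hoc testing may sit in an analysis plan that is not shown. The model, the role of week 0 and the reliance on the interaction are stated here, however, and can be judged as stated.

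**Conclusion.** The point holds as a matter of efficiency and of matching the test to the hypothesis; it should be fixed. Under the stated assumptions, the planned path declares a difference at week 6 or 12 in about 49-72% of trials (unadjusted post-hoc tests) or 51-93% (change scores), against about 84-97% for baseline-adjusted contrasts. The change-score loss nearly vanishes at correlation 0.7, while the unadjusted loss does not. Part of the loss comes from the assumed gate, as the no-gate comparison shows. Visit correlation and the week-26 effect are not in the document, so the size is a range and not a single figure.

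Two conclusions do not depend on those assumptions. The interaction can be significant because of week 26 alone. And the expectation of no group main effect does not follow from equality at baseline and conflicts with the hypothesised differences. That sentence changes no test, so it is an error of reasoning and not a threat to the result.

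**What to change.** Analyse PCSS at weeks 6, 12 and 26 with group, visit, group x visit, baseline PCSS and baseline x visit. Alternatively, keep week 0 as an outcome and constrain the group means to be equal there.

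Make the group differences at weeks 6 and 12 the primary contrasts, either each at 0.025 or as their average at 0.05, with week 26 supportive and no requirement for a significant interaction. The average has 92%, 95% and 99% power at correlations 0.3, 0.5 and 0.7 if the effect is 0.8 SD at both visits, but only 39%, 43% and 56% if it is confined to week 6. The choice should follow what the sponsor expects and be fixed before unblinding.

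Use the same baseline adjustment for NPRS, NDI, HDI and DHI. Delete the sentence "We expect no group effects, as the groups should be equal at baseline".

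The cost is analysis wording: no extra participants, visits or data, since baseline PCSS is already collected. The small downside is one covariate to estimate per visit and no single omnibus p-value.

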## Methods

### Study design

This single-blind, parallel-group RCT will include 8 supervised treatments during a 6-week rehabilitation program and four evaluation sessions over 26 weeks (baseline, week 6 [immediately after the rehabilitation program], week 12 [6 week after the end of the rehabilitation program] and week 26). All participants will take part in the baseline evaluation. After giving informed consent, they will first complete a questionnaire on sociodemographic (age, gender, type of sport or physical activities, number of years playing sport and/or other activities), symptomatology (mechanism of injury, history of previous mTBI, history of dizziness, headache, neck pain and unsteadiness) and comorbidity, as well as self-administered questionnaires that evaluate symptoms and functional limitations, including the PCSS (primary outcome). Once baseline data are collected, participants will be randomly assigned to a control or an experimental group. The control group will receive a 6-week gradual sub-threshold physical activation (SPA) program. The experimental group will receive a gradual SPA program combined with a cervicovestibular rehabilitation program. Between week 6 and week 12, participants will be asked to continue their exercises and follow the advice given at the last meeting with the health professional. Six, 12 and 26 weeks after randomization, all the outcomes will be revaluated (see Table 1). The evaluation sessions will be carried out at the *Centre interdisciplinaire de recherche en réadaptation et en intégration sociale* (CIRRIS) by a research assistant blinded to group assignment, while the interventions will be given at *Clinique Cortex* by experienced physiotherapists, neuropsychologists and kinesiologists. Recruitment began on April 1st 2019 in Quebec City, Canada. See Table 1 for Schedule of enrolment, interventions, and assessments. Ethics approval has been obtained from the Sectorial Rehabilitation and Social Integration Research Ethics Committee of the CIUSSS-CN (#2018–619)*.* The study protocol has been registered on ClinicalTrials.gov [NCT03677661–09/15/2018 - version 1].

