#### *Inclusion criteria*

Between 18 and 65 years of age;Sustained a mTBI in the past 3 to 12 weeks;Having ongoing post-concussion symptoms from the list in the PCSS that started 72 h or less after an impact;Having felt at least one or more of the following cognitive symptoms: lost of consciousness for less than 30 minutes following the trauma, feeling slowed down, feeling like in a fog, “don’t feel right”, difficulty concentrating, difficulty remembering and confusion that started 72 h or less after an impact;Having abnormalities on one of the following tests: the cervical physical examination (eg, tenderness/spasm/pain on segmental testing, or reduced motion), the vestibular evaluation (eg, Dix halpike test, vestibulo-ocular reflex test, or head thrust test) or the ocular motor evaluation (eg, convergence, smooth visual pursuits, or saccades).

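### Days to clearance are compared with an independent t-test, although participants who are not cleared have no value and no rule covers them

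*Protocol article*

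**What the plan says.** The section on clearance to return to function defines the outcome as "The number of days between the initial evaluation, the date of the trauma and the full clearance to return to function". The clearance day is the day on which three conditions hold together: symptoms are back at their usual level, the impairments found at the start "will be considered in the normal range by the treating therapist", and "the subject returned to his normal level of all functional activities".

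The Statistical analyses section names the test without qualification: "An independent t-test will be used to analyse the effects of the rehabilitation programs on clearance to return to function". The same section promises: "An intention-to-treat analysis will be used in which all participants will be analysed in the group to which they were originally assigned". The article gives no censoring rule and no substitute value for a participant without a clearance date.

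On timing, the Study design section sets "four evaluation sessions over 26 weeks" and says that all outcomes are measured again at weeks 6, 12 and 26. The control-group section adds: "If the symptoms disappear within the treatment period, the subject will be evaluated for clearance". The experimental-group section says the same for that arm.

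**The concern.** Time to clearance is a time-to-event outcome. A participant who has not met all three conditions when observation ends has no number of days, and neither does one who drops out first. A t-test needs a number for everyone it compares, so it must either omit these participants or use a value that the article does not supply.

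Such participants are to be expected. Eligibility ("Sustained a mTBI in the past 3 to 12 weeks", with symptoms still present) selects people who are slow to recover, and the sample size allows for 10% attrition.

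Omitting them selects on something that happens after randomisation. An arm that brings more slow recoverers to clearance adds long times to its own average, while the other arm's uncleared participants drop out of sight. The stated hypothesis includes a faster return to activities, and this is the outcome that measures it.

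**Working it through.** **The plan's own figure.** The article gives no power or expected rate for clearance. The 23 per group is derived for the PCSS and does not bear on this point. All rates below are assumptions.

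**Inputs.** Follow-up is τ = 26 × 7 = 182 days (Study design). There are 21 per arm: 23 × 0.9 = 20.7 after 10% attrition (Population). Assumed: exponential clearance times, a hazard ratio of 2 in favour of the experimental arm, and 95%, 75% or 50% of controls cleared by day 182.

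**What a t-test on cleared participants compares.** With p the proportion of controls cleared, the control rate is λ = −ln(1 − p)/τ, and the experimental rate is 2λ.

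- Mean time among the cleared = 1/λ − τ·e^(−λτ)/(1 − e^(−λτ))
- Restricted mean to day 182, all participants = (1 − e^(−λτ))/λ

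For p = 0.75, λ = 1.3863/182 = 0.007617 and 1/λ = 131.3. In the experimental arm the proportion cleared is 1 − 0.25² = 93.75% and 1/(2λ) = 65.6.

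- Among the cleared: control 131.3 − 182 × 0.25/0.75 = 70.6 days; experimental 65.6 − 182 × 0.0625/0.9375 = 53.5 days; difference −17.1 days.
- Restricted mean: control 0.75 × 131.3 = 98.5 days; experimental 0.9375 × 65.6 = 61.5 days; difference −36.9 days (before rounding).

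The comparison of cleared participants therefore shows 17.1/36.9 = 46% of the restricted-mean effect. The table gives the same formulas for the other rates. Power is from simulation at the two-sided 5% level, counting significant results in favour of the experimental arm.

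| Controls cleared | Experimental cleared | Difference among cleared (days) | Restricted-mean difference (days) | t-test, cleared only | Log-rank |
|---|---|---|---|---|---|
| 95% | 99.75% | −21.3 | −27.4 | 44% | 57% |
| 75% | 93.75% | −17.1 | −36.9 | 18% | 54% |
| 50% | 75% | −10.0 | −32.8 | 8% | 44% |

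**If uncleared participants are assigned day 182.** In the 75% case the t-test then has about 50% power against 54% for log-rank. Most of the loss comes from omitting participants.

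**When the sign can turn.** Simulated with 23 per arm. Suppose 50% of each arm clear at a mean of about 60 days, and the experimental treatment brings a further 40% to clearance at about day 110. The experimental mean among the cleared is (0.5 × 60 + 0.4 × 110)/0.9 = 82.2 days against 60, although that arm does better. In simulation the difference was +21.6 days. The t-test was significant in the wrong direction in 33% of trials, while log-rank favoured the experimental arm in 64%. With 70% v 95% cleared, the difference was +13.1 days.

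**If everyone clears** (means 60 v 90 days), both tests have 77% power.

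**Time origin.** The definition names both the initial evaluation and the trauma. Injury lies 3 to 12 weeks (21 to 84 days) back at entry. If that interval were uniform, counting from trauma would add a standard deviation of 63/√12 = 18.2 days that treatment cannot influence. Randomisation balances it in expectation, so it adds variance, not bias.

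**The case against.** The strongest reply is that the article never says uncleared participants are dropped. It promises that all participants will be analysed, and the trial team could assign the last day of follow-up, which recovers most of the power. This is right as far as it goes, and it rules out claiming that the plan keeps only recovered participants. But no such rule is written, and the last day would not be a true value for someone who left earlier. The planned check of distributional assumptions does not help either, because censoring is not a matter of distributional shape.

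A reader might also infer that clearance is assessed only during the 6-week programme, so that most times would be censored at day 42. The intervention sections say what happens if symptoms disappear during treatment; they do not say that clearance is assessed only then. The clearance section sets no time limit, and all outcomes are measured again to week 26. It remains true that no clearance procedure after week 6 is spelled out.

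A third tempting reading is that the effect will be hidden or reversed. Under proportional hazards the effect shrinks on average but keeps its direction, and a significant result in the wrong direction occurs in under 1% of trials. With no treatment effect at all, the test on cleared participants rejected in 4 to 6% of trials.

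Finally, clearance is one of several secondary outcomes. That stands, and it limits the severity.

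**Conclusion.** The point holds: the article fixes a method that does not fit the variable, and it cannot be reconciled with the intention-to-treat statement unless everyone clears or an unstated value is assigned. Because the test is named outright, this is more than a detail left to a fuller analysis plan.

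The size depends on clearance rates that the documents do not give. Under the assumptions above, power on cleared participants falls short of log-rank by 13 percentage points (57 − 44) when 95% of controls clear and by 36 points when 75% (54 − 18) or 50% (44 − 8) clear. Reversal needs extra late recoveries in the experimental arm. Little or nothing is lost if everyone clears.

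This should be fixed, but it does not threaten the trial's main result: the outcome is secondary, and the sample size and primary conclusion rest on the PCSS.

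**What to change.** Replace the t-test with Kaplan-Meier curves and a log-rank test or Cox model, stratified by sex (the randomisation stratum), in all randomised participants. Set time zero at baseline/randomisation. Censor uncleared participants at last contact or at the end of the period in which clearance is assessed, at most week 26, and state that period. Report the restricted mean difference in days with its confidence interval. Keep days since trauma as a descriptive figure.

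The cost is one paragraph of analysis wording and a recorded censoring date for each uncleared participant. No new measurements and no change of design are needed.
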